#### Initial acupuncture physician

The initial acupuncture physician will provide patients in the two acupuncture groups with the initial acupuncture and education program.

#### Secondary acupuncture physician

The secondary acupuncture physician will verify the allocated group while the patient lies prone during needle retention from initial acupuncture, and administer *Shinbaro* pharmacopuncture or secondary acupuncture accordingly. The second physician will administer acupuncture and pharmacopuncture in a similar manner in terms of advice and manual stimulation, and limit conversation to that absolutely necessary for the procedure to maintain patient-blinding, treat the patient out of view of the initial physician, remove the additional acupuncture needle immediately, and cover the area with adhesive bandage to maintain physician-blinding.

#### Usual care physician

The usual care physician will prescribe the patient with case-appropriate treatments from the predetermined list of physical therapy and conventional medicine. If the patient was taking pain medication before trial participation, the usual care physician will consider prescribing the same dose of the same ingredient(s), and patients in the usual care group may be prescribed additional conventional medicine.

#### Outcome assessor

The outcome assessor will assess all outcomes at all time points (except adverse event assessments) in a separate room, and will not discuss treatment group allocation with the patient.

### Blinding

The outcome assessor and statistician will be blinded to the three different treatment types, and the patient and initial acupuncture physician will be blinded to the two acupuncture groups. If possible, visiting times will be scheduled so as to avoid patient contact between groups. The secondary acupuncture physician will not record any information in patient charts for secondary acupuncture-blinding in the initial acupuncture physician, patient, outcome assessor, statistician, and study monitoring agent. All researchers will be impartial towards each patient, and will not try to become knowledgeable of patient allocation. The acupuncture, pharmacopuncture, usual care, and patient education program will be conducted according to the predetermined standard operating procedure (SOP). Blinding will be maintained for study duration, and all data will be collected and transferred from paper case report forms to electronic data processing at study completion. Data will be cross-checked for accuracy, and all data will be non-accessible to all researchers except the statistician. A blinding test will be conducted to assess successful blinding in the two acupuncture group participants and the initial acupuncture physician after the second treatment session.

### Interventions

#### Initial acupuncture

Acupuncture will be administered by KMDs who have received 1) 6 years of university education, and 2) 4 years of specialist training at a Ministry of Health and Welfare-certified institution, or 3) have at least 3 years’ clinical experience at a Ministry of Health and Welfare-designated spine-specialty Korean medicine hospital.

The KMDs will receive five training sessions before trial initiation for standardized acupuncture administration following detailed SOP instructions. The acupuncture physicians and physician in charge of patient management in the usual care group will record symptoms and any recent changes in the patient chart at each visit, and conduct the once weekly education programs. The education program will inform the patient of the favorable prognosis of LDH, and give instructions for everyday activities and self-management. The education program will consist of handbooks, with weekly reminders and encouragement from the physician. However, the physician will maintain a neutral stance in answering questions about the effect of each treatment modality. KMDs assigned with patient education will also receive five prior training sessions to ensure homogeneity in education content. The 2 acupuncture groups will undergo a total 8 sessions of acupuncture, 2 sessions/week for 4 weeks. Disposable sterile needles (40 mm × 0.25 mm; Dong-bang Acupuncture, SeongNam, Korea) will be used. The initial acupuncture physician will mark 1 *Hyeopcheok* (*Huatuo Jiaji*, EX B2) point most relevant to patient symptoms with reference to the MR image using an indelible surgical skin marker (Viscot, East Hanover, NJ, USA) with an “x,” and will not administer acupuncture to that point but use 5 acupoints for needling (GB30, BL40, BL25, BL23, GB34) as recommended in the “Korean Medicine Clinical Practice Guideline for Lumbar Herniated Intervertebral Disc in Adults” [17]. The 5 points will be disinfected with disposable 70 % isopropyl alcohol cotton swabs, and needled to about 1-cm depth assisted by an acupuncture guide tube with no manual stimulation such as twirling or lifting and thrusting. In selecting left or right side in the 5 acupoints, GB30, BL40, and GB34 will be needled on the side with sciatic symptoms, and BL25 and BL23 on the contralateral back region. The reason for contralateral needling is to avoid overlapping with the area marked for secondary acupuncture or *Shinbaro* pharmacopuncture. The secondary acupuncture physician will disinfect the marked area with a povidic saturated swabstick (Gumi Pharma, Gimpo, Korea) using gradually expanding circular strokes to about a 5-cm radius. Needle retention will be standardized at 20 minutes. The initial acupuncture physician will leave a piece of paper marked with the patient’s random allocation number on the bed for the secondary acupuncture physician. The patient will remain in the prone position during acupuncture.

#### Secondary acupuncture –- Shinbaro pharmacopuncture group

The secondary acupuncture physician will administer pharmacopuncture at the acupoint marked by the initial physician in the *Shinbaro* pharmacopuncture group with no contact with the disinfected area. The secondary acupuncture physician will prepare for treatment by loading a disposable Kovax-syringe (20 ml, 23G x 1″; Korea Vaccine, Ansan, Korea) with 6 cc of refrigerated *Shinbaro* pharmacopuncture solution (prepared at Jaseng herbal medicine dispensary, an extramural facility meeting Korean Good Manufacturing Practice (K-GMP) standards), and replacing the syringe needle with a smaller gauge disposable needle (26G x 1 1/2″; Jung Rim, Jincheon, Korea).

The secondary acupuncture physician will recheck the allocation number and determine whether the povidone has dried, and after accessing the tissue perpendicularly at the marked area to a depth of 4 cm with the 4 cm needle, will slowly inject 6 cc of the solution. The physician will immediately remove the inserted needle while applying pressure to the surrounding tissue to reduce bleeding, and then apply pressure with dry sterilized gauze for about 15 seconds. A povidic saturated swabstick will be used for disinfection with gradually increasing circular strokes to about a 5 cm radius, and prevent wound infection with a Superpore wound dressing adhesive (9 cm x 12 cm; Band Gold, Gwangmyeong, Korea) with the added effect of concealing the area from the physician who will remove the other needles.

#### Preparation of Shinbaro pharmacopuncture

*Shinbaro* pharmacopuncture solution will be prepared at Jaseng herbal medicine dispensary following KMD prescription of a herbal medicine compound containing GCSB-5 (Eucommia ulmoides cortex, Acanthopanax sessiliflorum cortex, Achyranthis bidentata radix, Saposhnikovia divaricata radix, Cibotium barometz rhizoma), whose main properties of anti-inflammation, cartilage protection, and nerve regeneration have been demonstrated in vivo and in vitro, and Paeonia albiflora radix alba, Ostericum koreanum radix, Angelica pubescens radix, and Scolopendra subspinipes corpus (*Paeonia albiflora* twice the proportion of that of other ingredients). The ingredients will be extracted using reflux extraction with 70 % *spiritus vinosus*, then purified progressively (80 %, 90 %) using alcohol immersion and freeze-dried. The freeze-dried powder will be mixed and dissolved in filtered normal saline (0.9 % NaCl), filtered at 0.2 μm for microorganism removal, packaged in vials sealed with rubber stoppers, and sterilized at 121 °C for 15 minutes. Only end-products that have passed quality control inspection, such as microbe cultivation and contamination tests, will be used.

The freeze-dried powder concentration to be used in pharmacopuncture will be set at 1.178 mg/ml, which is within the interval of optimal anti-inflammatory effects and non-apoptosis in in vitro tests, and which has been tested in vivo for single-dose toxicity in beagle dogs and single-week and 4-week multiple dose toxicity in rats at a Good Laboratory Practice institution.

#### Secondary acupuncture – acupuncture group

The secondary acupuncture physician will administer acupuncture at the acupoint marked by the initial physician in the acupuncture group, accessing the tissue perpendicularly at the marked area to a depth of 4 cm using a disposable sterile needle (40 mm × 0.4 mm; Dong-bang Acupuncture, SeongNam, Korea) without an acupuncture guide tube, and with no contact with the disinfected area. The physician will adopt a manner highly similar to *Shinbaro* pharmacopuncture in method, procedure and timing to maintain patient-blinding. The physician will also use needle twisting to evoke soreness similar to injection of solution, and inform the patient that solution injection may cause soreness. The physician will immediately remove the inserted needle while applying pressure to the surrounding tissue to reduce bleeding, and then apply pressure with dry sterilized gauze for about 15 seconds. A povidic saturated swabstick will be used for disinfection with gradually expanding circular strokes to about a 5 cm radius, and prevent wound infection with a Superpore wound dressing adhesive with the added effect of concealing the area from the physician who will remove the other needles.

Administration of secondary acupuncture (*Shinbaro* pharmacopuncture or acupuncture) will take place within the 20-minute initial acupuncture needle retention.

#### Usual care

The usual care physician will provide patients with conventional medicine and physical therapy referring to a list of most frequently used treatments in patients with a primary diagnosis of LDH (KCD: M51, M541) from Health Insurance Review and Assessment (HIRA) 2011 statistics. Frequency and contents of medicine and physical therapy use will be recorded.

#### Co-interventions

Provision of LDH treatment (surgery, nerve blocks, other acupuncture, physical therapy, etc.) other than the interventions listed above will not be allowed. However, a maximum of 4 g of acetaminophen may be provided as rescue medication to all participants, and use will be recorded.

### Outcomes

The detailed time points of each outcome assessment index are listed in Table 1.

**Table 1 Tab1:** Time points of each assessment index

Week	Screening (baseline)	1		2		3		4		5	7	9	12
Visit	1	2	3	4	5	6	7	8	9	10	11	12	13
Informed consent	o												
Demographic characteristics, Medical history	o												
Inclusion/Exclusion criteria	o												
Blood test	o									o			o
MRI	o												o
Credibility and Expectancy Questionnaire	o												
Blinding test				o									
Randomization		o											
Treatment		o	o	o	o	o	o	o	o				
Education program		o		o		o		o		o	o	o	o
NRS	o	o	o	o	o	o	o	o	o	o	o	o	o
VAS		o		o		o		o		o	o	o	o
ODI		o		o		o		o		o	o	o	o
Physical examination		o		o		o		o		o	o	o	o
SF-36		o								o	o		o
EQ-5D		o								o	o		o
PGIC										o	o		o
Safety assessment		o	o	o	o	o	o	o	o	o	o	o	o
Use of medication		o	o	o	o	o	o	o	o	o	o	o	o

EQ-5D EuroQol-5 Dimension, MRI magnetic resonance imaging, ODI Oswestry Disability Index, NRS, Numeric Rating Scale, PGIC patient global impression of change, SF-36 Short Form Health Survey 36, VAS Visual Analog Scale

#### Primary outcome measurement

The primary outcome will be intensity of sciatic pain as measured by the Visual Analog Scale (VAS). VAS uses a 10-cm line labeled at each end with scale anchors [18]. In pain measurement, patients are asked to mark a point that represents their pain between the anchors of “no pain” and “worst pain possible” (labels vary by study). Scores are recorded in millimeters with a total range of 0–100 mm [19]. As pain intensity may differ at rest and during activity, to reduce error patients will be asked: “Please rate the pain intensity you feel during daily activities.”

#### Secondary outcome measurements

Secondary outcomes will include intensity of LBP measured with VAS, and will likewise try to reduce error with the following question: “Please rate the pain intensity you feel during daily activities.”

LBP and sciatic pain intensity will also be assessed with NRS. Although NRS is considered to be a subjective index, it is widely used for its simplicity. In pain measurement, patients are asked to rate their pain by selecting a number from 0 to 10 that best represents their current pain severity (0 is “no pain”, and 10, “worst pain possible”) [20, 21].

Functional impairment will be evaluated using the accredited Korean version of the Oswestry Disability Index (ODI) [22]. The ODI is a 10-item questionnaire developed to assess level of disability due to LBP [23]. Each item is graded into 6 levels, each representing a score of 0–5. Higher scores indicate greater limitation relating to LBP.

For a more comprehensive evaluation of improvement in pain and functional disability, patient global impression of change (PGIC) will be assessed [20, 24]. PGIC grades the level of subjective improvement into 7 levels (1, very much improved; 2, much improved; 3, slightly improved; 4, no change; 5, slightly worse; 6, much worse; and 7, very much worse).

Health-related quality of life (HRQoL) of LDH will be assessed using the Short Form Health Survey 36 (SF-36) and EuroQol-5 Dimension (EQ-5D). SF-36 consists of 36 items across 8 domains: physical functioning, role-physical, bodily pain, general health, vitality, social functioning, role-emotional, and mental health [25]. SF-36 is used to rate functional health and well-being in patients and healthy individuals. Han et al. verified the reliability and validity of the Korean version of SF-36 in measuring HRQoL in aged Korean patients [26]. Higher scores indicate better HRQoL. EQ-5D is a tool developed for HRQoL assessment, and is widely used in the health care sector. Scores range from −1, “health worse than death” to 1, “perfect health” [27]. EQ-5D has 5 dimensions covering current health status and functionality: mobility (M), self-care (SC), usual activities (UA), pain/discomfort (PD), and anxiety/depression (AD), to be rated out of 3 grades (1, no problem; 2, some/moderate problem; 3, extreme problem). We will use weighted values in calculating EQ-5D, applying a weighted model for Koreans [28]:$$ \begin{array}{c}\hfill EQ-5D\  index=1-\left(0.050+0.096\times M2+0.418\times M3+0.046\times SC2+0.13\times SC3+0.051\times UA2\right.\hfill \\ {}\hfill \left.+0.028\times UA3+0.037\times PD2+0.151\times PD3+0.043\times AD2+0.158\times AD3+0.050\times N3\right)\hfill \end{array} $$

M2, SC2, UA2, PD2, and AD2 will be assigned values of 1 if a grade 2, and 0 if not. M3, SC3, UA3, PD3, and AD3 will be assigned values of 1 if a grade 3, and 0 if not, and N3 a value of 1 if any of the 5 EQ-5D items is a grade 3, and 0 if not. Also, if all 5 EQ-5D items are grade 1, the EQ-5D index will be 1.

Range of movement (ROM) and straight leg raise (SLR) tests will be conducted to assess improvement following treatment. ROM measurements are valid (*r* = 0.97) and reliable (*r* = 0.94), [29] but not highly responsive (effect size = 0.1–0.6) [30]. While SLR measurements are reliable (intraclass correlation coefficient = 0.95), [31] with a sensitivity of 0.8 (72–97 %) and specificity of 0.4 (11–66 %), [32] they are also not very responsive (effect size = 0.2) [30]. If ROM is uncheckable from pain, the angle will be recorded as 0°.

Expectations of treatment will be assessed with the Credibility and Expectancy Questionnaire which uses a 9-point Likert scale [33]. Participants will be asked the following question at first visit (1, “not at all”; 5, “somewhat”; and 9, “very much”): “To what extent do you expect pharmacopuncture, acupuncture, and usual care therapy to relieve your symptoms?”

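### The printed EQ-5D formula gives extreme problems with usual activities a smaller decrement (0.028) than moderate problems (0.051), so some health states are misordered if it is used as printed

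*Protocol article*

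**What the plan says.** Under Secondary outcome measurements, the protocol article defines the five EQ-5D items as "to be rated out of 3 grades (1, no problem; 2, some/moderate problem; 3, extreme problem". It then commits to a scoring rule: "We will use weighted values in calculating EQ-5D, applying a weighted model for Koreans", citing a Korean valuation (reference 28). The equation follows in full. The constant, mobility and self-care terms are "0.050+0.096\times M2+0.418\times M3+0.046\times SC2+0.13\times SC3". The grade 2 weight for usual activities appears in "0.13\times SC3+0.051\times UA2" and the grade 3 weight in "0.028\times UA3+0.037\times PD2". The remaining terms are "0.037\times PD2+0.151\times PD3+0.043\times AD2+0.158\times AD3+0.050\times N3".

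The coding rules are explicit. For grade 2, "M2, SC2, UA2, PD2, and AD2 will be assigned values of 1 if a grade 2, and 0 if not", and the grade 3 indicators are defined in the same way. The extra term is "N3 a value of 1 if any of the 5 EQ-5D items is a grade 3, and 0 if not". An all-grade-1 profile scores 1. Higher values mean better health.

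The Statistical analysis section lists EQ-5D among the secondary outcomes to be analysed by analysis of covariance, as for the primary outcome. Table 1 schedules it at visit 2 and at weeks 5, 7 and 12.

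**The concern.** The grade 2 and grade 3 indicators exclude each other. A patient who moves from moderate to extreme problems with usual activities therefore exchanges a decrement of 0.051 for one of 0.028. Taken alone, that says extreme problems are less bad than moderate ones. The article neither explains this nor gives another value elsewhere, and no other dimension behaves this way.

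The formula is a stated scoring rule for a declared outcome. Programmed as printed, it would record some deteriorations as gains and some improvements as losses, and would understate other changes. The trial is also a pilot meant to prepare a larger one, so an uncorrected formula could be carried forward.

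**Working it through.** **Inputs**, all from the printed equation: constant 0.050; N3 0.050; and these weights:

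| Dimension | Grade 2 | Grade 3 | Grade 3 minus grade 2 |
|---|---|---|---|
| Mobility (M) | 0.096 | 0.418 | +0.322 |
| Self-care (SC) | 0.046 | 0.13 | +0.084 |
| Usual activities (UA) | 0.051 | 0.028 | **-0.023** |
| Pain/discomfort (PD) | 0.037 | 0.151 | +0.114 |
| Anxiety/depression (AD) | 0.043 | 0.158 | +0.115 |

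Only usual activities has a negative difference.

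**Effect of moving usual activities from grade 2 to grade 3**

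- Another item already at grade 3 (N3 already counted): change = 0.051 - 0.028 = **+0.023**. The index rises.
- No other item at grade 3 (N3 switches on): change = 0.051 - 0.028 - 0.050 = **-0.027**. The index falls, but only because of N3.

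**Worked states** (order M, SC, UA, PD, AD)

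- 22232: 1 - (0.050 + 0.096 + 0.046 + 0.051 + 0.151 + 0.043 + 0.050) = 1 - 0.487 = 0.513
- 22332: 1 - (0.050 + 0.096 + 0.046 + 0.028 + 0.151 + 0.043 + 0.050) = 1 - 0.464 = 0.536, a worse state with a higher score
- 33233: 1 - (0.050 + 0.418 + 0.13 + 0.051 + 0.151 + 0.158 + 0.050) = 1 - 1.008 = -0.008
- 33333: 1 - (0.050 + 0.418 + 0.13 + 0.028 + 0.151 + 0.158 + 0.050) = 1 - 0.985 = 0.015, so the worst state is not the minimum
- 22222 = 0.677 and 22322 = 0.650: no other item at grade 3, and the index falls by 0.027

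**All states.** The other four items have 3^4 = 81 combinations, of which 2^4 = 16 contain no grade 3. Scoring all 243 states confirms that the step from UA2 to UA3 raises the index in 81 - 16 = 65 combinations and lowers it in 16. The same step in each of the other four dimensions gives 0 reversals of 81. The minimum over all states is -0.008.

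**What a correction would do.** The documents do not give the right value. With UA2 held at 0.051, any UA3 of at least 0.051 removes every reversal. The score of 33333 is then 0.043 - UA3. For assumed UA3 values of 0.051, 0.100, 0.151, 0.200 and 0.250 it is -0.008, -0.057, -0.108, -0.157 and -0.207, against 0.015 as printed.

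**Effect on an arm comparison.** If UA3 is the wrong weight, the difference in mean index shifts by (true UA3 - 0.028) × (difference between arms in the proportion at grade 3). Assume 2 more of 20 patients at that grade in one arm, a proportion difference of 0.10:

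- true UA3 = 0.051: 0.023 × 0.10 = 0.002
- true UA3 = 0.100: 0.072 × 0.10 = 0.007
- true UA3 = 0.250: 0.222 × 0.10 = 0.022

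With equal proportions the shift is zero.

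**The case against.** The strongest reply is that the formula transcribes a cited valuation, and that a slip in the article need not be present in the scoring program. That stands: the documents do not show that the EQ-5D result will be wrong, only that it will be if the printed formula is used. It does not remove the point, because the text commits the trial to these weights.

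A reader might also draw four stronger conclusions that the documents do not support.

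- **That most affected patients are scored in reverse.** The count of 65 in 81 is over theoretical combinations weighted equally. Participants are outpatients aged 25 to 55. If grade 3 mobility and self-care are assumed absent, 20 of 36 combinations reverse; if grade 3 anxiety/depression is also assumed absent, 8 of 24 do. No state frequencies are given. The entry criterion of sciatic NRS 5 or higher makes extreme pain plausible but says little about usual activities.
- **That the arm comparison is biased.** Every arm is scored with the same formula, so the mean difference moves only if the frequency of the mis-scored grade differs by arm.
- **That the self-care weight is truncated.** SC3 is printed as 0.13 where the other weights have three decimals. It may simply be 0.130, it exceeds SC2, and it causes no reversal.
- **That UA3 is certainly the wrong coefficient.** It is the likelier one, since 0.028 lies below every printed grade 2 weight (the smallest is 0.037). The article alone cannot exclude an error in UA2.

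**Conclusion.** The point holds in conditional form. Scored as printed, the index misorders states that differ only in moderate versus extreme problems with usual activities: by +0.023 when another item is at grade 3, with a fall of only 0.027 otherwise, and with 33333 not at the minimum. This follows from the article's own coefficients and coding rules and needs no outside figure.

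Taking UA3 as the faulty weight, index values are wrong for patients at grade 3 usual activities and for no others. Their number, and so the size and direction of any effect on an arm difference, cannot be known from the documents. The consequence is confined to one secondary outcome of a 60-patient pilot; the VAS primary outcome does not depend on the formula. Provided the item responses are kept, the index can be recomputed without loss. It should be fixed, but it does not threaten the trial's main result.

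**What to change.** - Before any scoring, compare the usual-activities weights with the Korean valuation cited as reference 28, and correct the formula in the protocol and the scoring program. The value must come from that source, not from the range shown above. SC3 can be confirmed in the same comparison.
- Add an automatic check over all 243 states that no worsening of a single item raises the index and that 33333 has the minimum value.
- If any index values have already been computed with the printed weights, recompute them from the item responses.

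The cost is one comparison with the source, probably one changed coefficient, and a few lines of code. Nothing changes for patients, visits or data collection.
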